# Study protocol of a cluster-randomised controlled trial assessing a multimodal machine-based exercise training programme in senior care facilities over 6 months – the bestform study (best function of range of motion)

**DOI:** 10.1186/s12877-023-04176-7

**Published:** 2023-08-22

**Keywords:** Frailty, Sarcopenia, Resistance training, Retirement homes, Ageing, Falls, Exercise

## Abstract

**Background:**

Physical functioning is a crucial factor for independence and quality of life in old age. The aim of the "bestform—Best function of range of motion" trial is to investigate the effects of a 6 months multimodal machine-based strength, coordination and endurance training on physical function, risk of falls and health parameters in older adults.

**Methods:**

Bestform is a cluster-randomised trial including older adults  ≥ 65 years living in senior care facilities in Southern Germany. Senior care facilities are randomly allocated to the control group with usual care (*n* ≥ 10 care facilities) and to the intervention group (*n* ≥ 10 care facilities), overall including  ≥ 400 seniors. Residents belonging to the intervention group are offered a supervised machine-based exercise training programme twice weekly over 45–60 min over six months in small groups, while those in the usual care facilities will not receive active intervention. The primary outcome is the change in Short Physical Performance Battery over six months between groups. Secondary outcomes are change in risk of falling, fear of falling, number of falls and fall-related injuries, physical exercise capacity, handgrip strength, body composition, cardiac function, blood parameters, quality of life, risk of sarcopenia, activities of daily living, and cognition over three and six months.

**Discussion:**

The bestform study investigates the change in physical function between seniors performing exercise intervention versus usual care over six months. The results of the study will contribute to the development of effective physical activity concepts in senior care facilities.

**Trial registration:**

ClinicalTrials.gov: NCT04207307. Registered December 2019.

**Supplementary Information:**

The online version contains supplementary material available at 10.1186/s12877-023-04176-7.

## Background

Due to the demographic change, the ageing society faces individual and common health challenges. On the one hand, life expectancy has increased significantly in Germany and most European countries in recent decades [1]. On the other hand, today’s inactive lifestyle is leading to a significant increase in lifestyle diseases [2] such as hypertension, coronary heart disease or type 2 diabetes and raises the risk of needing long-term care [3] in old age.

Physical inactivity is common in older adults, especially when living in senior care facilities [4], and is responsible for a deterioration in physical performance. One example for impaired physical performance is a reduction of gait speed, which is a determinant to be able to perform daily tasks and to maintain independent [5–7]. Moreover, reduced activity and subsequently reduced muscle strength is also associated with geriatric syndromes such as sarcopenia [8] and frailty [9], increased osteoporosis, risk of falls and increased fracture rates. About 30% of individuals over the age of 65 years report at least one fall per year [10]. Falls increase the fear of repetitive falls leading to a vicious circle of reduced mobility, decline in physical performance and further increase of risk of falls [11].

It has been shown that the participation in effective, multimodal exercise programmes with strength, coordination and balance training can counteract this vicious cycle and can improve physical function, mental well-being, quality of life, and reduce the risk of falling in older adults with or without comorbidities [12–18]. Adaptation of muscle strength by training has even been shown in 70–82 year-old individuals [14]. Therefore, detailed recommendations for exercise interventions are available for older adults [19–21].

However, larger randomised-controlled trials involving very old individuals beyond 80 years applying structured exercises are rare. Particularly machine-based exercises have not extensively been investigated in this patient cohort on a large scale. Moreover, the setting of senior care facilities seems to be ideal for introducing exercise interventions. On the basis of our pilot study (bestform-F; 77 residents; 74–103 years, 85.6 ± 6.6 years; 78% women) that has shown feasibility of a multimodal machine-based strength, balance and endurance training, [22] we have designed the “Bestform-trial – Best Function of Range of Motion”; hereinafter referred to as “bestform”, to examine the efficacy of this training on physical function and risk of falls as well as assessing safety of the intervention. The training programme is performed over a 6-month period in at least 20 senior care facilities in a cluster-randomized setting. The primary endpoint is the Short Physical Performance Battery (SPPB) after 6 months.

## Methods/design

### Design and participants

The prospective cluster-randomised, controlled, two-armed study is organised and conducted by the Department of Prevention and Sports Medicine (Technical University of Munich, Germany). The participating senior care facilities (≥ 10 intervention senior care facilities,  ≥ 10 control senior care facilities) are randomly allocated to one of the two study groups. The participants of the intervention senior care facilities are provided with a physical training programme (“bestform-training”). The participants of the control senior care facilities will not receive any training intervention (usual care), but are provided with information meetings/brochures on a healthy lifestyle. In each intervention senior care facility a machine-based exercise training equipment is installed after randomisation.

The hypothesis of the bestform-trial is that a 6 months multimodal exercise training (machine-based strength, coordination and endurance training) is superior to usual care regarding Short Physical Performance Battery (SPPB) in residents aged ≥ 65 years living in senior care facilities. Secondary endpoints are outlined in Table 2 and obtained on site at three different time points: at baseline, after three months, and after six months. Afterwards, follow-up data will be collected after 18 and 30 months by questionnaires. The study flowchart is illustrated in Fig. 1. Our study protocol is in line with the SPIRIT 2013 statement for clinical trial protocols [23] and subsequent trial reporting considers the CONSORT recommendations for clinical trial reporting [24].

**Fig. 1 Fig1:**
[figure not shown]
CONSORT Flow diagram showing the bestform-study design and the flow of the participants

The study has been approved by the local ethics committee of the University Hospital “Klinikum rechts der Isar”, Technical University of Munich, Germany (548/19 S-SR). The study is registered under ClinicalTrials.gov (NCT04207307).

### Recruitment of senior care facilities

Senior care facilities are recruited in the Munich area. A local media campaign and personal telephone calls to senior care facilities will draw attention to the study. A total of 20 senior care facilities is projected, but if the aimed number of participants of  ≥ 400 is not reached, then further facilities will be included until this number is met. Eligibility criteria for senior care facilities include adequate space for implementing exercise facilities and commitment of the general manager of the senior care facility to take part in the study. Study sites include senior homes, offering assisted living as well as caring areas covering the whole spectrum of level of care. Senior care facilities are advised that participation into the trial does not automatically imply participation into the intervention arm. Aside, senior care facilities should preferably have  ≥ 100 residents and an expected participation rate  ≥ 20 residents. Furthermore, no regular machine-based strength training should have been installed. However, care facilities should have the space to set up a fitness facility for a machine-based exercise training programme.

### Allocation of senior care facilities

Participating senior care facilities are allocated randomly to one of the two study groups based on a computer-generated list. Permuted block technique is used to generate group assignments (1:1). The list is stored at the Institute of AI and Informatics in Medicine (AIIM) of the University Hospital “Klinikum rechts der Isar”, Munich, Germany (former Institute for Medical Informatics, Statistics and Epidemiology, IMedIS). Group allocation is performed based on the randomisation list. Individuals involved in the recruitment process and in communication with the senior residences do not have access to the randomisation list.

Allocated senior care facilities are informed whether they have been assigned to intervention or usual care. Thereafter, in intervention senior care facilities, equipment of machine-based exercise training is installed.

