### Study participants

Members permanently living in selected homes are informed and invited to participate in the study by an information meeting or personal communication by staff. In case of general participation agreement to be assigned to usual care or intervention, individuals will be informed about the planned investigations including the potential training intervention. To participate in the study, a written informed consent is mandatory to be signed by the study participant or her/his legal representative.

Thereafter, medical history and physical examinations are performed on site (examination 1) in all individuals to assess for inclusion and exclusion criteria. For inclusion, study participants need to be able to stand independently without assistance and be physically and mentally able to participate in the study based on the judgement of the physician performing the clinical examination. Exclusion criteria comprise any acute or chronic illness or physical/mental condition as well as any dementia disease, which does not allow to stand independently or which does not allow physical training in small groups or which would require a training under supervision. All participants have to pass the medical examination including ECG and echocardiography. For this a 12-lead resting electrocardiography (ECG) is conducted to exclude pathologic conditions. This will be added by an echocardiography (ECHO) (CX50, Philips, Netherlands/USA) to assess pathologies e.g. impaired myocardial function or valvular heart disease that pose contraindications for exercise training. Moreover, blood is drawn for analysis of cardio-metabolic risk factors (e.g. blood lipids, blood glucose), safety parameters (e.g. electrolytes, creatinine), parameters of inflammation and acute infection (e.g. high sensitive C-reactive protein) as well as brain natriuretic peptide (pro-BNP) for heart failure screening. Blood samples are stored for future analyses.

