Secondary endpoints will be analysed in an exploratory manner. For continuous data, observed means and standard deviations will be presented for both study groups and tests for group differences will be performed as described for the primary analysis. Absolute and relative frequencies for both groups will be presented for binary outcomes. Group comparisons will be conducted by fitting marginal logistic regression models with study group as independent variable to the data accounting for within cluster correlations (generalised estimating equation, GEE models). For count data (e.g. number of falls) corresponding Poisson regression models or negative binomial models will be used. Kaplan–Meier curves will be drawn to illustrate distributions of time-to-event data (time to first MACE) for both study groups. For group comparisons, a Cox regression model with fixed effect for study group and robust standard errors considering the clustering will be fitted to the data. Estimated hazard ratios with corresponding 95% confidence intervals will be presented. Observed adverse events and serious adverse events will be listed and frequencies of adverse events and serious adverse events will be presented. Proportions of individuals with at least one adverse event will be compared between study groups using a logistic GEE model accounting for clustering.

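### The event models contain study group only, so with about 20 homes allocated without a named stratum they give up precision and leave a chance imbalance in residents' frailty uncorrected

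*Protocol article*

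**What the plan says.** Protocol article, *Recruitment of senior care facilities*: "A total of 20 senior care facilities is projected", with more added if 400 participants are not reached. On the kind of home: "Study sites include senior homes, offering assisted living as well as caring areas covering the whole spectrum of level of care".

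Protocol article, *Allocation of senior care facilities*: "Permuted block technique is used to generate group assignments (1:1"). No stratification factor or other balancing constraint is named.

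Protocol article, *Statistical analysis*: the primary mixed model has study group, baseline SPPB and a random home effect, and continuous secondary outcomes follow the same approach. Binary outcomes are analysed by "fitting marginal logistic regression models with study group as independent variable to the data accounting for within cluster correlations". Time to first MACE uses "a Cox regression model with fixed effect for study group and robust standard errors considering the clustering will be fitted to the data". Mortality and hospitalisation over 6 months are listed under *Secondary outcomes*. The status of all these analyses is given as "Secondary endpoints will be analysed in an exploratory manner".

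**The concern.** Permuted blocks equalise the number of homes per arm. They do nothing to equalise how frail the residents are. For SPPB and the other measured scales, the baseline term repairs much of any imbalance. Death, hospitalisation and MACE have no baseline value of their own, and the models written out for event outcomes put nothing in its place. Prognosis is therefore adjusted for in one family of outcomes and ignored in the other.

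The article makes safety a stated aim and links later implementation to the training proving safe and effective. Deaths and hospital admissions will be read as part of that safety result, whatever their formal status. With about 10 homes per arm, two things are at stake: an apparent harm or benefit that merely reflects which homes fell into which arm, and avoidable loss of power in comparisons that rest on few events.

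**Working it through.** **1. The plan's own figure.** d = 1/2.5 = 0.4 at 5% two-sided and 80% power needs 99 to 100 per group (plan: 100). Design effect = 1 + (25 − 1) × 0.025 = 1.60. 100 × 1.6 = 160 per group, and 320/0.8 = 400. The sample size reproduces. It is set for SPPB and is not affected by this point.

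**2. How often would a clear imbalance arise?** Assumption, not in the article: 10 of 20 homes are higher risk. The number falling in one arm is hypergeometric, P(k) = C(10,k)²/C(20,10), with C(20,10) = 184,756.
- 6:4 or worse: 1 − 63,504/184,756 = 0.66
- 7:3 or worse: 2 × (1 + 100 + 2,025 + 14,400)/184,756 = 0.18
- 8:2 or worse: 2 × (1 + 100 + 2,025)/184,756 = 0.023

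Simulated blocks of 2 and 4 also give 0.18 for 7:3 or worse. With 4, 6 or 8 higher-risk homes, the chance that the arms differ by four or more such homes is 0.087, 0.14 or 0.17.

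**3. What would a 7:3 split do with no treatment effect?** Arm risks are 0.7 × high + 0.3 × low against 0.3 × high + 0.7 × low. All event risks are assumed.

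| Low / high risk | Arm risks | Odds ratio |
|---|---|---|
| 2% / 4% | 0.034 vs 0.026 | 1.32 |
| 5% / 10% | 0.085 vs 0.065 | 1.34 |
| 4% / 12% | 0.096 vs 0.064 | 1.55 |
| 5% / 15% | 0.120 vs 0.080 | 1.57 |

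The shift can go in either direction. If the homes do not differ in risk, the odds ratio is 1.0.

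**4. Average and conditional behaviour of the unadjusted model.** Null simulation with 20 homes of 20 residents, 10 of them higher risk, 20,000 runs, logistic GEE with independence working correlation and sandwich error:
- Mean log odds ratio: 0.00 in every scenario.
- SD of the log odds ratio: 0.51 at 3%/9%, against 0.45 at a uniform 6%. The variance ratio is (0.51/0.45)² ≈ 1.3.
- Type I error: 0.074 to 0.077 with unequal homes, 0.069 with equal homes. Most of the excess over 0.05 therefore comes from having few clusters. A small-sample correction (variance × 10/9, t on 18 df) brings it to 0.040 to 0.048.
- False-positive rate when the split is 7:3 or worse: 0.17 (3%/9%), 0.20 (5%/15%), 0.30 (10%/30%). When the split is even: 0.04, 0.03, 0.01.

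**5. Scale against sampling error.** At 4%/12% and 200 per arm, a 7:3 split means 0.096 × 200 = 19.2 against 0.064 × 200 = 12.8 deaths. The SE of the log odds ratio is √(1/19.2 + 1/180.8 + 1/12.8 + 1/187.2) = 0.376, giving a 95% interval of about 0.74 to 3.2 even before clustering.

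**6. What adjustment buys.** In a simulation of 20 homes of 20 residents with assumed risks and about 18 to 110 events, adding baseline SPPB and age raised the power of the logistic model by about 3 to 22 percentage points, with type I error near 5%. The gain depends on how strongly the two covariates predict the event; if they predict it only weakly, it shrinks towards nothing.

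**7. Can the data carry two more terms?** At a mean risk of 8% (4%/12%), 400 × 0.08 = 32 deaths, or 32/3 ≈ 11 events per model term. At 3% (2%/4%) there are 12 events, or 4 per term, which is too thin to rely on.

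**The case against.** **Bias.** A reader might infer that unstratified allocation distorts the mortality, hospitalisation and MACE comparisons. The documents do not support that. Randomisation leaves the estimate unbiased on average, and the GEE and the cluster-robust Cox errors already carry between-home variation: 4%/12% implies an ICC of 0.0016/0.0736 = 0.022 and a design effect of 1 + 19 × 0.022 ≈ 1.4, ordinary clustering. This objection stands. What remains is that a robust error widens the interval without moving an estimate shifted by the realised split, and that unadjusted models are less precise.

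**Type of home.** A reader might also infer that some homes are assisted living and others nursing homes. The recruitment sentence can equally mean that each home contains both, so the 10:10 split is an illustration only. Eligibility narrows the range further: "study participants need to be able to stand independently without assistance", and they must pass a medical examination. This stands too, and it weakens the case for a facility stratum. It does not weaken resident-level adjustment, which works under either reading.

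**Attribution and status.** Only MACE is tied to a named model. The logistic GEE for mortality is inferred from the rule for binary outcomes, and a rate of hospitalisation could fall under the count models. The analyses are exploratory, and a full protocol or analysis plan may add strata or covariates. All true. Yet the article does write these event models out, with study group as the only stated term, so the point concerns a stated choice and not an omitted detail.

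**Cost.** Extra terms are not free when events are few. This stands and limits the fix.

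**Conclusion.** The point holds in a limited form. No stratum is named for about 20 homes, and the event models are written with study group only, while the other models adjust for a baseline value. The comparisons are valid on average. With about 10 homes per arm, however, a chance imbalance in frailty can mislead in the one trial that is run, and precision is given up without need.

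The size cannot be fixed from the article. The 18% chance of a 7:3 or worse split, the null odds ratios of 1.32 to 1.57 and the conditional false-positive rates of 0.17 to 0.30 all rest on half the homes being higher risk and on assumed event risks. The power gain of 3 to 22 points rests on assumed risks and covariate strength. None of this shows that the allocation method is wrong or that stratification is required. The sample size and the primary analysis are unaffected.

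**What to change.** In *Statistical analysis*, add baseline SPPB and age, both available from the baseline examination, as covariates in the event models for mortality and hospitalisation. Add them to the Cox model for MACE where event counts allow. State beforehand the event count below which the adjusted model is dropped, and show the unadjusted result beside every adjusted one. Naming the model used for mortality and for hospitalisation would remove the present ambiguity.

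Cost: two model terms and no new data. The adjusted odds and hazard ratios are conditional on the covariates and will not equal the unadjusted ones even with perfect balance, so the labels must say so. For sparse outcomes such as MACE, the adjusted model may have to be dropped.

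Optional: stratify homes not yet allocated by a facility-level care factor and keep that factor in the models. This is worthwhile only if homes really differ in care type, and it is moot once allocation is complete. If the full protocol already stratifies, it is enough to say so and carry the factor into the event models.

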### Study participants

Members permanently living in selected homes are informed and invited to participate in the study by an information meeting or personal communication by staff. In case of general participation agreement to be assigned to usual care or intervention, individuals will be informed about the planned investigations including the potential training intervention. To participate in the study, a written informed consent is mandatory to be signed by the study participant or her/his legal representative.

Thereafter, medical history and physical examinations are performed on site (examination 1) in all individuals to assess for inclusion and exclusion criteria. For inclusion, study participants need to be able to stand independently without assistance and be physically and mentally able to participate in the study based on the judgement of the physician performing the clinical examination. Exclusion criteria comprise any acute or chronic illness or physical/mental condition as well as any dementia disease, which does not allow to stand independently or which does not allow physical training in small groups or which would require a training under supervision. All participants have to pass the medical examination including ECG and echocardiography. For this a 12-lead resting electrocardiography (ECG) is conducted to exclude pathologic conditions. This will be added by an echocardiography (ECHO) (CX50, Philips, Netherlands/USA) to assess pathologies e.g. impaired myocardial function or valvular heart disease that pose contraindications for exercise training. Moreover, blood is drawn for analysis of cardio-metabolic risk factors (e.g. blood lipids, blood glucose), safety parameters (e.g. electrolytes, creatinine), parameters of inflammation and acute infection (e.g. high sensitive C-reactive protein) as well as brain natriuretic peptide (pro-BNP) for heart failure screening. Blood samples are stored for future analyses.

### Intervention

The multimodal bestform-intervention consists of a machine-based resistance, coordination and endurance training, which is performed twice per week for 45–60 min in intervention senior care facilities. Age and disability adapted pneumatic resistance training machines (HUR Health and Fitness Equipment, HUR, Finland) are used, including easy access devices for wheelchair users, targeting large muscle groups (leg extension/curl rehab, leg press rehab, push up/pull down EA, chest press EA, optimal rhomb EA).

The exercise is conducted under supervision of qualified exercise instructors (sports scientists, fitness trainers with additional qualifications) and trained undergraduate assistants in small groups of 4 to 6 participants face-to-face in the intervention care facilities.

Prior to intervention start, the participants become familiarized with the exercise training within two introductory sessions (one per week). There, participants are introduced in handling of the machines and the correct execution of the exercises. Also, the entry level of the exercise loads is determined according to the individual´s condition.

Following, the bestform-training (two sessions per week) is carried out over six months and is structured into three phases: 1.) Accommodation phase, 2.) Regular exercise training and 3.) Intensified exercise training (Table 1). During these phases, exercise is increased in duration and intensity on an individual basis. For adaptation the BORG-Scale [25] is used corresponding to percent of 1-Repetition-Maximum (1-RM) [26].

**Table 1 Tab1:** Overview of the multimodal bestform-training intervention

	**Accommodation phase**		**Regular exercise training**		**Intensified exercise training**	
**Month**	1	2	3	4	5	6
**Duration**	45–60 min	45–60 min	45–60 min	45–60 min	45–60 min	45–60 min
**Frequency**	2x/week	2x/week	2x/week	2x/week	2x/week	2x/week
